# Advanced practice physiotherapy care in emergency departments for patients with musculoskeletal disorders: a pragmatic cluster randomized controlled trial and cost analysis

**DOI:** 10.1186/s13063-023-07100-x

**Published:** 2023-02-06

**Keywords:** Advanced practice physiotherapy, Physiotherapist, Emergency department, Musculoskeletal disorders, Primary care, Model of care, Economic analysis, Cost analysis

## Abstract

**Background:**

Advanced practice physiotherapy (APP) models of care where physiotherapists are primary contact emergency department (ED) providers are promising models of care to improve access, alleviate physicians’ burden, and offer efficient centered patient care for patients with minor musculoskeletal disorders (MSKD).

**Objectives:**

To compare the effectiveness of an advanced practice physiotherapist (APPT)-led model of care with usual ED physician care for persons presenting with a minor MSKD, in terms of patient-related outcomes, health care resources utilization, and health care costs.

**Methods:**

This trial is a multicenter stepped-wedge cluster randomized controlled trial (RCT) with a cost analysis. Six Canadian EDs (clusters) will be randomized to a treatment sequence where patients will either be managed by an ED APPT or receive usual ED physician care. Seven hundred forty-four adults with a minor MSKD will be recruited. The main outcome measure will be the Brief Pain Inventory Questionnaire. Secondary measures will include validated self-reported disability questionnaires, the EQ-5D-5L, and other health care utilization outcomes such as prescription of imaging tests and medication. Adverse events and re-visits to the ED for the same complaint will also be monitored. Health care costs will be measured from the perspective of the public health care system using time-driven activity-based costing. Outcomes will be collected at inclusion, at ED discharge, and at 4, 12, and 26 weeks following the initial ED visit. Per-protocol and intention-to-treat analyses will be performed using linear mixed models with a random effect for cluster and fixed effect for time.

**Discussion:**

MSKD have a significant impact on health care systems. By providing innovative efficient pathways to access care, APP models of care could help relieve pressure in EDs while providing efficient care for adults with MSKD.

**Trial registration:**

ClinicalTrials.govNCT05545917. Registered on September 19, 2022

## Administrative information

**Table Taba:** 

Title {1}	Advanced practice physiotherapy care in emergency departments for patients with musculoskeletal disorders: a pragmatic cluster randomized controlled trial and cost analysis
Trial registration {2a and 2b}.	ClinicalTrials.gov identifier: NCT05545917
Protocol version {3}	Version16, issue date: October 10, 2021
Funding {4}	This research is funded by the Canadian Institutes of Health Research (CIHR) (202010PJT-451693-CIB-CFCC-130299).


## Introduction

### Background and rationale {6a}

Overcrowding in emergency departments (ED) is one of the biggest concerns in several health care systems. This challenge will worsen in years to come given the aging populations, the increasing prevalence of chronic disorders, and physician shortages [1, 2]. Each year, there are almost 16 million visits made to Canadian EDs [3], and recent reports indicate that Canada is among the countries with the longest ED waiting times [3, 4]. Musculoskeletal disorders (MSKD) have been identified as one of the most prevalent disorders why persons consult EDs [2, 5–7]. Patients presenting to EDs with MSKD, such as tendinopathy, back pain, sprains, and osteoarthritis, could represent at least 25% of all visits [8, 9]. MSKD are also one of the most disabling and costly non-fatal health disorders [10, 11]. Currently, MSKD affect 11 million Canadians per year, and this number is expected to increase [12]. In Canada, MSKD are estimated to cost over 25 billion dollars per year [13].

Traditionally, ED physicians are the primary contact practitioners who manage patients with MSKD, although a high proportion of physicians report limited knowledge and confidence in taking charge of these patients [8, 14, 15]. Furthermore, these tasks deter ED physicians from managing patients with more serious conditions. Several initiatives have been implemented worldwide to improve not only access, but also quality of care for patients with MSKD [16]. New collaborative models of care integrating physiotherapists (PTs) in roles referred to as advanced practice physiotherapy (APP) have been emerging in various settings, such as orthopedic clinics and EDs. PTs in Canada have long had direct access [17] to patients for traditional rehabilitation as they have extensive expertise in MSKD care [18]. Traditionally, PTs provided care in EDs only after physicians assessed patients and made a referral for physiotherapy care. APP models of care in EDs allow for collaborative practice with physicians that is aimed to benefit ED performance, patient care, and outcomes, as well as health care resource usage. In these roles, PTs can also triage patients and, in some jurisdictions, order medical imaging or prescribe/deprescribe certain medications, in addition to providing recommended non-pharmacologic interventions for the management of MSKD [19]. Studies have shown that APP care for MSKD, such as low back pain, significantly decreases opioid prescriptions and long-term use [20–22]. In countries such as Australia and the United Kingdom (UK), integrating APP care in the ED has shown to improve wait times and quality of care for patients with MSKD [23], with high patient and ED physician satisfaction [24–28]. While models of APP care in the ED are emerging globally, none of these models has been evaluated in Canada, where these models are also emerging.

### Objectives {7}

Thus, the aim of our project is to evaluate the impact of an APP-led model of care compared to usual physician ED care for persons presenting with minor MSKD. The specific objectives are:To compare the effectiveness of both types of care in terms of patient-related outcomes for patients with minor MSKD in six Canadian EDs, at discharge from the ED and 4, 12, and 26 weeks after the ED consultation, on the following outcomes:Primary outcome: the Brief Pain Inventory (BPI) – Interference of pain on function subscaleSecondary outcomes: pain intensity, disability, patient satisfaction with care, and adverse events.To compare health care resource utilization between both types of care at ED discharge and at 4, 12, and 26 weeks after the initial consultation, including proportion of ED return visits for the same complaint, medication prescriptions, prescriptions for imaging and laboratory tests, and referral to other health care providersTo compare both types of care in terms of health care costs from the public payer’s perspective and perform a cost-utility analysis, at ED discharge and at 4, 12, and 26 weeks after the initial consultationTo compare wait to initial assessment and ED length of stay between both types of care for the evaluation and treatment of participants during their ED visit

We hypothesize that integrating APP-led care in the ED will be at least as effective as usual ED physician care for patients with a MSKD, in terms of patient-related and health care resource utilization-related outcomes. Furthermore, health care costs will be lower in the APP-led care arm.

### Trial design {8}

This project is a multicenter pragmatic stepped-wedge (3 steps with 4 periods of 6 weeks each) cluster RCT with a cost analysis conducted in six Canadian EDs.

## Methods: participants, interventions, and outcomes

### Study setting {9}

Patients will be recruited from the following six Canadian EDs: Maisonneuve-Rosemont Hospital (MRH) (CIUSSS-de-l’Est-de-l’Ile-de-Montréal, Montréal, Québec), Centre Hospitalier Universitaire de l’Université Laval (CHUL) and Enfant-Jésus Hospital (EJH) (CHU de Québec, Québec), Hotel-Dieu Hospital (Kingston Health Sciences Center-KHSC, Kingston, Ontario), Hôtel-Dieu Hospital (CIUSSS-de-l’Estrie-CHUS, Sherbrooke, Québec), and Rockyview General Hospital (Calgary, Alberta).

### Eligibility criteria {10}

The inclusion criteria are (1) patients presenting with complaints related to minor MSKD (e.g., back pain, joint sprain, osteoarthritis, muscle pain, or tendinopathy) triaged as level 3, 4, or 5 on the Canadian Triage and Acuity Scale (CTAS); (2) aged 18 years or more; (3) legally able to consent; (4) able to understand/speak French or English; and (5) be a beneficiary of a provincial universal health insurance coverage.

The exclusion criteria are (1) having injury resulting from major trauma (e.g., high-velocity trauma or major motor vehicle accident); (2) presenting a major musculoskeletal injury (e.g., open fractures, unreduced dislocations, open wounds, or a condition that needs an urgent surgical intervention); (3) presenting a red flag (e.g., progressive neurological deficits or infection-related symptoms); (4) consulting for a diagnosed inflammatory arthritis or other active/unstable non-musculoskeletal condition (e.g., pulmonary, cardiac, digestive or psychiatric condition); and (5) consulting for a work-related MSKD eligible for workers’ compensation benefits.

### Who will take informed consent? {26a}

Research professionals in each site will explain the study, including the purpose and the required implication by participants, to eligible patients and will answer any remaining questions. Research professionals will then obtain written informed consent from patients who agree to enroll in this study. Information and consent forms will be available in both French and English, depending on the participants’ preferred language.

### Additional consent provisions for collection and use of participant data and biological specimens {26b}

N/A, no ancillary studies

### Interventions

#### Explanation for the choice of comparators {6b}

In the Canadian health care system, patients presenting to EDs will receive the usual care from an ED physician. As this is the most prevalent model of care for patients with MSKD, this will be used as our control arm.

#### Intervention description {11a}

The experimental arm will receive APP-led care. Patients will be independently managed (assessment and intervention) by a PT (*n* = 12, two per site). The PT will make a diagnosis and initiate an intervention plan (e.g., education and exercise). If relevant, the PT will make recommendations for medical imaging tests or medication. PTs will also recommend the proper discharge from the ED, such as hospitalization, discharge without medical consultation/follow-up, or discharge with a medical follow-up or rehabilitation in an outpatient setting. To ensure that these medical recommendations made by PTs in respect of the current professional legislations, an independent ED physician, not participating in the usual care arm, will be present in the ED and will be available to ensure the required medical care according to the PTs intervention plan (e.g., prescribe medication/tests/referrals) if needed. In the event that modification to the plan is found necessary (i.e., only if found unsafe for the patient) by the independent ED physician, this will be recorded and secondary analyses including only participants with no plan modifications will be performed.

The control arm will receive the usual ED physician care delivered by an ED physician. This will include independent assessment, treatment, and discharge by an ED physician with no physiotherapy within the ED but a physician’s referral to outpatient physiotherapy or other professionals/medical specialists will be possible. Overall care offered by the ED physician will not be standardized but will be systematically documented.

Participants in both arms presenting a non-MSKD condition after assessment will be excluded from the study. The proportion of excluded participants per group, as well as the reasons for exclusion, will be systematically collected and analyzed (Fig. 1).

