### Sample size {14}

The main hypothesis is that APP-led care will be at least as effective as usual ED physician care based on the results of our literature review [16] and ED studies [43, 44]. The sample size required is based on a target effect size of 0.35, using the primary outcome measure, the BPI short form, with a two-sided significance level of 0.05 and a power of 0.80. An intra-cluster correlation coefficient of 0.004 was assumed based on a prior cluster RCT that also used the BPI short form as a primary outcome [55]. The calculation further assumed 6 clusters with an exchangeable correlation structure within clusters, a total of 3 sequences (steps), and two clusters changing treatment per sequence. With these assumptions, the trial will be adequately powered if 27 individuals are accrued per cluster per sequence. Hence, we will recruit 31 patients per site per sequence, accounting for a potential loss to follow-up of 15%. The total sample of 744 participants (124 per site) will provide an adequate sample size to meet our objectives.

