## Statistical methods

### Statistical methods for primary and secondary outcomes {20a}

Descriptive statistics will be used to present the participants’ characteristics. Baseline demographic data will be compared across groups and the participating EDs to establish the comparability of study samples across intervention arms and clusters. If differences are observed, statistical models will be adjusted, and any difference will be considered. Descriptive statistics will be computed for all outcome measures at different measurement times. Per-protocol and intention-to-treat analysis will be performed. Outcomes will be analyzed at the individual level using mixed models as recommended for stepped-wedge designs [56]. A linear mixed model with a random effect for cluster and fixed effects for the intervention status and time period will be used for continuous outcomes including the primary outcome (BPI score). Separate analyses will be conducted on each of the secondary outcomes. In the case of non-normal outcomes, including re-visits and adverse events, a generalized linear mixed-model framework will be used. Time-driven activity-based costing (TDABC) will be the methodology used to capture the costs of providing services to achieve primary and secondary outcomes. TDABC’s micro-costing approach will allow us to precisely determine and differentiate the cost of providing care based on the specific types of patients. Measuring patient outcomes and costs to achieve those outcomes will provide a more rigorous approach to understanding the value of introducing innovative modifications to existing clinical pathways. This approach has the potential to compare costs, outcomes, and clinical pathways within single health care institutions, among regional care centers and across provinces.

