#### Adverse event reporting and harms {22}

The current literature on the safety of ED physiotherapy care with MSKD patients found no increase in adverse events associated with ED physiotherapist-led care [16, 43]. Moreover, physiotherapists will systematically present to an independent ED physician requests for medical imaging and diagnostic tests, medication prescription, or referrals to other providers, to respect medical legislation and ensure safety. Any adverse events will be documented and fully detailed. They will also be communicated to the CIUSSS-de-l’Est-del’Ile-de-Montréal Ethics Committee and reviewed by the co-principal investigators and co-investigators.

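### The no-plan-modification secondary analysis can remove patients only from the APP arm, on a safety ground, so its between-arm contrast is not between comparable groups

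*Protocol article*

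**What the plan says.** All of this is in the protocol article.

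- **APP arm, Intervention description {11a}.** The physiotherapist manages the patient, and "an independent ED physician, not participating in the usual care arm, will be present in the ED" to provide the medical acts that the plan requires. The trigger for a change is narrow: "In the event that modification to the plan is found necessary (i.e., only if found unsafe for the patient) by the independent ED physician". Changes are recorded, and "secondary analyses including only participants with no plan modifications will be performed".
- **APP arm, Adverse event reporting and harms {22}.** The review is routine: "physiotherapists will systematically present to an independent ED physician requests for medical imaging and diagnostic tests, medication prescription, or referrals to other providers".
- **Usual care, Intervention description {11a}.** "This will include independent assessment, treatment, and discharge by an ED physician with no physiotherapy within the ED". No second provider reviews the plan.
- **Analysis sets, Statistical methods {20a}.** "Per-protocol and intention-to-treat analysis will be performed". The article does not say who belongs to the per-protocol set.
- **Target, Sample size {14}.** "The sample size required is based on a target effect size of 0.35", for the BPI.

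**The concern.** Membership of the restricted set depends on an event that happens after allocation, can happen in only one arm, and consists of a judgement that the arm's own plan was unsafe. Every usual-care participant meets the criterion automatically, because nothing in that arm could be recorded as a modification. Patients whose physiotherapist plan was judged unsafe leave the APP arm. Patients of the same kind seen by physicians stay in, as do any unsafe physician plans, since no one is assigned to detect them. Provisions for post-trial care {30} names diagnostic error by either type of provider as the main risk, so the filter acts on that risk in one arm only.

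The same section treats its other post-assessment exclusion, a non-musculoskeletal condition, symmetrically in both arms. The plan-modification rule has no such counterpart.

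At stake is how the result is read. The hypothesis is that APP care is at least as effective as usual care, and a restricted estimate that leans towards APP could look like support for it. The risk is larger if the rule also becomes the definition of the per-protocol set.

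**Working it through.** **1. Reproduce the plan's own figure.** Inputs from Trial design {8} and Sample size {14}: I = 6 clusters, T = 4 periods, 3 sequences of 2 clusters, 27 evaluable patients per cluster-period, ICC 0.004, effect 0.35 (taken in SD units, total SD 1), two-sided 0.05.

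Hussey-Hughes variance = I·s²·(s² + T·τ²) / [(I·U − W)·s² + (U² + I·T·U − T·W − I·V)·τ²]

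- s² = 0.996/27 = 0.03689; τ² = 0.004
- U = 12 treated cluster-periods; W = 0 + 4 + 16 + 36 = 56; V = 2 × (9 + 4 + 1) = 28
- Numerator: 6 × 0.03689 × (0.03689 + 0.016) = 0.01171
- Denominator: 16 × 0.03689 + 40 × 0.004 = 0.7502
- Variance = 0.01560, SE = 0.1249 SD
- Power = Φ(0.35/0.1249 − 1.96) = Φ(0.842) = 0.80, as stated
- Recruitment: 31 × 4 × 6 = 744, of whom 12 × 31 = 372 are expected in APP and 372 in usual care

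**2. Who can be excluded.** Only the 372 APP patients; none of the 372 usual-care patients.

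**3. Size of the shift.** Let q be the share of APP patients with a modified plan, and D the mean BPI gap (modified worse than unmodified, in SD). The mean of all APP patients is the unmodified mean plus q·D. Dropping the modified patients therefore moves the contrast towards APP by

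shift = q × D

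The protocol gives neither q nor D, so both are assumptions. A share of 5-20% would be about 19 to 74 of the 372.

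| q | D = 0 | D = 0.3 | D = 0.5 | D = 0.8 |
|---|---|---|---|---|
| 5% | 0 | 0.015 (4%) | 0.025 (7%) | 0.040 (11%) |
| 10% | 0 | 0.030 (9%) | 0.050 (14%) | 0.080 (23%) |
| 20% | 0 | 0.060 (17%) | 0.100 (29%) | 0.160 (46%) |

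Entries are in SD; brackets give the share of the 0.35 target.

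**4. Effect on error rates.** With no true effect, the chance of a nominally significant result in favour of APP is about Φ(shift/0.1249 − 1.96), against a nominal 2.5%:

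- shift 0.025: 3.9%
- shift 0.05: 5.9%
- shift 0.10: 12.3%
- shift 0.16: Φ(1.281 − 1.96) = Φ(−0.679), about 25%

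This uses the SE of the full set; the restricted set is slightly smaller.

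**5. Simulation check.** The stepped-wedge mixed model was simulated with a true effect of 0, known variances and 1,000 runs per scenario. A negative mean estimate favours APP.

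| q, D | Mean, all patients kept | Mean, restricted set | False APP-better rate, restricted |
|---|---|---|---|
| 5%, 0.5 | 0.002 | −0.024 | 3.1% |
| 10%, 0.5 | 0.000 | −0.050 | 6.3% |
| 10%, 1.0 | −0.001 | −0.102 | 12.3% |
| 20%, 0.5 | 0.003 | −0.095 | 10.2% |
| 10%, 0 | 0.006 | 0.005 | 2.5% |

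With all patients kept, the false-positive rate was 2.1-2.7%. The simulated shifts agree with q × D, and the shift vanishes when D = 0.

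**The case against.** The strongest reply has five parts.

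- **The analysis is labelled secondary, and intention-to-treat is kept.** This stands, and it limits the severity. Nothing in the protocol makes the restricted set the basis for the main conclusion.
- **The direction is assumed.** A reader might infer that the bias must run towards APP for pain, costs and safety alike. The documents do not show that. The physician intercepts the plan before harm is done, and a patient who has had input from both providers may do as well as anyone else. For BPI and costs the direction is the expected one and no more.
- **The size is assumed.** This also stands. The upper end, 46% of the target, needs both extreme inputs together. The Discussion reports high diagnostic agreement and no serious pathology missed in the team's earlier concordance study, and eligibility excludes red flags and major injury, so a low share is plausible. At 5% and 0.3-0.5 SD the shift is 4-7% of the target, small against an SE of 0.125 SD. A reader might also infer that most APP adverse events would be removed. Nothing in the documents indicates that adverse events would concentrate in modified patients.
- **The comparator is not spelled out.** True, but on the plain wording every usual-care participant qualifies. The control-arm statement "Overall care offered by the ED physician will not be standardized but will be systematically documented" concerns standardization and recording; it supplies no review from which a matching control subset could be drawn. A summary within the APP arm alone would escape the criticism.
- **How patients fare when the physiotherapist's plan stands is a fair question.** It is, and that is a reason to allow a descriptive display. It does not justify an inferential contrast with unselected controls.

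**Conclusion.** The point holds as a defect in a stated analysis rule, not as missing detail. The exclusion is one-sided, post-allocation and tied to safety, so the restricted between-arm contrast does not compare like with like, whatever its numerical size. For the BPI it is expected, not certain, to favour APP by q × D: 0-0.16 SD for an assumed 5-20% modified and a gap of 0-0.8 SD. There is no shift at all if modified patients do no worse.

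Two stronger conclusions are not supported. The trial's main result is not compromised, because the intention-to-treat analysis does not use this restriction. Nor does the protocol say that this restriction is the per-protocol set; it leaves that set undefined in the article, and the concern is only that this rule could fill the gap. A change of wording is warranted; removing all mention of the subset is more than is needed.

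**What to change.** 1. Keep participants with modified plans in the APP arm for all inferential between-arm comparisons: effectiveness, safety, resource use and costs.
2. State that the no-modification restriction does not define the per-protocol set named in Statistical methods {20a}.
3. Report the number of modifications and the reasons for them, with an exact 95% confidence interval for the proportion, as a process and safety outcome of the APP arm.
4. If the restricted set is shown at all, label it descriptive and draw no conclusion on effectiveness or safety from it.

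The cost is a few sentences in the protocol or analysis plan. The modification data are already to be recorded, and neither the sample size nor trial conduct changes. The price is that the trial gives up an inferential estimate for physiotherapist plans that stood unaltered.

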#### Criteria for discontinuing or modifying allocated interventions {11b}

No specific criteria for modifying allocated interventions were defined since this is a punctual intervention. However, participants in both arms presenting a non-MSKD condition after assessment will be excluded from the study and will receive usual ED physician care outside the trial according to their condition.

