#### Provisions for post-trial care {30}

The main potential risk in this trial is a diagnostic error by PTs or physicians. Any adverse events will be documented within the current study, and we will ensure study participants receive the appropriate care if needed.

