### Recruitment {15}

All new patients presenting to participating EDs and triaged by nurses (based on the usual triage process used in each ED) as having a possible MSKD will be considered for this study. In addition, a research professional in each site will screen the triage lists to identify any other potential participants for the trial and ensure none are omitted. Eligibility of ED patients will subsequently be assessed regarding the inclusion and exclusion criteria during an in-person interview with a research professional and review of medical records. Research professionals will explain the study to eligible patients and obtain their informed consent.

For patients who decline participation in the project, demographic data, such as age, sex, reason for consultation, and reason to refuse to participate, will be collected to calculate participation proportions and establish comparisons between participants and non-participants.

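### Consented participants are excluded on the result of an assessment that differs by arm, which the promised intention-to-treat analysis does not accommodate

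*Protocol article*

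**What the plan says.** Recruitment {15} places eligibility and consent with research staff before any provider is involved: "Research professionals will explain the study to eligible patients and obtain their informed consent". Table 1 likewise puts screening and consent at enrolment, ahead of the post-evaluation time point.

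Intervention description {11a} then describes the two assessments. In the experimental arm, "The PT will make a diagnosis and initiate an intervention plan (e.g., education and exercise". Of the control arm it says: "This will include independent assessment, treatment, and discharge by an ED physician". The same section states the rule: "Participants in both arms presenting a non-MSKD condition after assessment will be excluded from the study". It adds that the proportion excluded in each group and the reasons will be collected and analysed. Section {11b} repeats the rule, saying that such patients will be "excluded from the study and will receive usual ED physician care outside the trial according to their condition".

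Section {17a} says that neither participants nor providers are blinded. Section {20a} states: "Per-protocol and intention-to-treat analysis will be performed". It does not say how the exclusion fits with the second of these. Section {30} states: "The main potential risk in this trial is a diagnostic error by PTs or physicians".

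**The concern.** Removing ineligible patients after allocation can be defended when the judgement does not depend on allocation. Here it may. A PT's assessment and an ED physician's assessment need not recognise non-musculoskeletal conditions at the same rate, and that assessment is part of what the trial compares. Who stays in the dataset can thus be a consequence of the arm.

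Three things are at stake:

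- **Intention-to-treat.** An analysis without these patients does not include everyone allocated.
- **Secondary objectives.** Recognised non-MSKD cases take their length of stay, cost, ED re-visits and adverse events out of the comparison, while unrecognised cases stay in. Re-visits, costs and length of stay are all objectives in {7}, and adverse events are a listed secondary outcome.
- **Recoverability.** The rule governs participation as well as analysis. If excluded patients are not followed at 4, 12 and 26 weeks, a later analysis plan cannot restore their outcomes.

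**Working it through.** **1. The plan's own figure.** Inputs from Sample size {14}: 6 clusters, 3 steps with 2 clusters switching at each, effect size 0.35, ICC 0.004, two-sided alpha 0.05, power 0.80, 27 per cluster-period. The 4 periods are from Trial design {8}. The Hussey-Hughes variance, with total variance 1, I = 6 clusters, T = 4 periods, s² = (1 − 0.004)/n and t² = 0.004, is

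Var = I·s²·(s² + T·t²) / [(I·U − W)·s² + (U² + I·T·U − T·W − I·V)·t²]

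For this layout:
- U = 2×(3+2+1) = 12
- W = 0² + 2² + 4² + 6² = 56
- V = 2×(9+4+1) = 28

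The two coefficients are 72 − 56 = 16 and 144 + 288 − 224 − 168 = 40.

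At n = 27, s² = 0.996/27 = 0.03689 and Var = 6×0.03689×0.05289 / (16×0.03689 + 40×0.004) = 0.01171/0.7502 = 0.0156, so SE = 0.1249. Power = Φ(0.35/0.1249 − 1.96) = 0.800. The stated 27 is reproduced.

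**2. Power if the exclusion stays.** The 15% in {14} is for loss to follow-up only. Evaluable n per site and period = 31 × 0.85 × (1 − x), where x is the assumed proportion excluded.

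| x (assumed) | n per site and period | Power | Recruits per site and period to keep 27 (total over 24) |
|---|---|---|---|
| 0 | 26.35 | 0.791 | 32 (768) |
| 2% | 25.82 | 0.784 | 33 (792) |
| 5% | 25.03 | 0.772 | 34 (816) |
| 10% | 23.71 | 0.752 | 36 (864) |

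The last column is 27/[0.85(1 − x)], rounded up. The first row is already below 0.80 because 31 is close to 27 × 1.15 = 31.05, whereas 27/0.85 = 31.8. That shortfall is separate from this point. The cost of the exclusion is the drop from 0.791: about 2 percentage points at 5% and 4 at 10%.

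**3. Shift in the BPI contrast.** Let e₁ and e₀ be the proportions excluded in the PT-led and control arms, and D the difference in mean 4-week BPI between excluded and retained patients, in SD units. In each arm the retained mean differs from the mean of everyone allocated by −e·D, so the contrast shifts by (e₀ − e₁)·D. The documents give neither e nor D. With assumed ranges:
- 2 points and 0.5 SD: 0.02 × 0.5 = 0.01 SD, or 3% of 0.35
- 5 points and 1 SD: 0.05 × 1.0 = 0.05 SD, or 14% of 0.35

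The sign depends on which arm recognises more cases and whether those patients do better or worse. Equal rates in both arms give no shift under this formula.

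**4. Length of stay, cost, re-visits and adverse events.** The documents give nothing from which to size the effect on these outcomes.

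**The case against.** The strongest defence is that the excluded group should be small and balanced. Eligibility {10} already screens out red flags and active or unstable non-musculoskeletal conditions, and {15} adds an interview and a record review. The Discussion reports high diagnostic agreement between PTs and physicians in the team's earlier study, with no non-MSKD pathology missed by the PTs. This makes a large difference between arms less likely but does not rule one out. Reporting exclusions and reasons by group will make an imbalance visible, but it will not supply the missing outcomes.

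The objectives concern minor MSKD, and the disability questionnaires are specific to body area. Keeping non-MSKD patients therefore slightly changes the population, and some instruments will not apply to them. That limits the fix without defeating it.

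The text also does not name who decides that a condition is non-MSKD. That it is the treating provider is inferred from the rule's placement after assessment and from the assessments described in {11a}.

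A reader might infer three stronger claims, which the documents do not support:

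- **That the rule removes the diagnostic errors named in {30} as the main risk.** A missed condition is the error, and it stays in follow-up, where {12} has adverse events, re-visits and incidents asked about at each time point and completed from medical files. The rule removes recognised cases. It sets no time limit on recognition, but nothing says that late-discovered cases are withdrawn.
- **That it biases wait to initial assessment through a second assessment.** Section {12} ends that wait at the first evaluation by either provider, so a later assessment cannot alter it.
- **That it is known to favour PT-led care.** A recognised case in that arm may use PT time and then physician time, but missed cases retained there could worsen its results. The net direction is not established.

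**Conclusion.** The point holds in a limited form. As written, {11a} and {11b} exclude consented participants on the result of an arm-specific, unblinded assessment, and {20a} promises an intention-to-treat analysis that would then omit some of those allocated. The conflict follows from the text, with one inference: that the assessment in question is the treating provider's.

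The size and direction of bias are unknown because no exclusion rate is given. Under the assumed ranges the BPI shift is modest, at most 0.05 SD, and the loss of power is about 2 to 4 percentage points for 5 to 10% excluded. The case for change rests more on the validity of the intention-to-treat set and on the length-of-stay, cost, re-visit and adverse-event comparisons than on the BPI. It should be fixed, preferably before follow-up begins, because outcomes not collected cannot be recovered.

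**What to change.** Reword the rule in {11a} and {11b} so that participants found to have a non-MSKD condition receive the care they need but remain in the trial. Follow them at 4, 12 and 26 weeks for BPI, EQ-5D-5L, re-visits, adverse events and costs, and keep their ED length of stay. Use the region-specific disability questionnaires only where they apply.

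In {20a}, include these participants in the intention-to-treat set under the arm in force at their site in that period. Report the analysis without them as a labelled sensitivity or per-protocol analysis, and keep the planned reporting of numbers and reasons by arm. The protocol already works this way for PT plans modified on safety grounds: {11a} records them and confines the restricted set to a secondary analysis.

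The cost is a change of wording, follow-up questionnaires for what is probably a small number of already-consented patients, and slight dilution of the minor-MSKD population. The planned 744 need not rise on account of these cases, since they no longer leave the analysis.
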